#### Analysis plan

The analyses of the primary and secondary endpoints will be performed in the FAS, which includes all patients who received at least one dose of treatment during the study period and did not have any serious violation of the study protocol, and had data collected after commencement of treatment. For the baseline characteristics, the summary statistics will comprise frequencies and proportions for categorical variables, and means and standard deviations for continuous variables. The patient characteristics will be compared using Chi square tests for categorical variables, and t tests for normally distributed continuous variables or Wilcoxon rank sum tests for continuous variables with a skewed distribution.

For the primary analysis comparing treatment effects, the least square mean and its 95 % confidence interval will be estimated using analysis of covariance (ANCOVA). To test for non-inferiority of the primary endpoint, the ANCOVA will be applied adjusted for age (<65, ≥65 year), HbA1c level (<6.5, ≥6.5 %), and left ventricular ejection fraction (LVEF; <40, ≥40 %). The secondary analysis will be performed in the same manner as the primary analysis.

All comparisons are planned and all *p* values will be two sided. *P* values <0.05 will be considered statistically significant. All statistical analyses will be performed using SAS software version 9.4 (SAS Institute, Cary, NC, USA). The statistical analysis plan will be developed by the principal investigator and a biostatistician before completion of patient recruitment and database lock.

Trial organization and oversight (details in Additional file 4).

Principal investigators of the CANDLE trial are [name] (Chief), Department of Cardiovascular Medicine, Saga University and [name], Department of Cardiology, Nagoya University Graduate School of Medicine. The Steering Committee will carry out planning, operating, analyzing, and presentation of the trial. The Executive Committee will supervise the trial design and operation of the study. The roles of DSMB and CEC are described in the section of Endpoint adjudication. The trial secretariat is in DOT INTERNATIONAL CO., LTD, Tokyo, Japan. Each of data management, monitoring, statistical analyses, and audit will be independently implemented on the basis of outsourcing agreement.

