## Methods

### Study overview and design

The CANDLE trial is an ongoing, multicenter, prospective, randomized, open-label, blinded-endpoint investigator-initiated clinical trial. This study tests the hypothesis that additional administration of canagliflozin to standard therapy does not worsen the pathological state of CHF, compared to the conventional anti-diabetic agent, glimepiride. Twenty-four weeks after recruitment and randomization into either canagliflozin or glimepiride groups, the safety and non-inferiority of canagliflozin for T2DM patients with CHF will be evaluated using NT-proBNP as a biomarker of heart failure.

Prior to initiation, the study protocol needs to be approved by the local institutional review boards and independent ethics committees at every site. The trial will be conducted in full compliance with the Declaration of Helsinki and according to the Ethical Guidelines for Medical and Health Research Involving Human Subjects established by the Ministry of Health, Labour, and Welfare and Ministry of Education, Culture, Sports, Science, and Technology.

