### Safety

Based on the intention-to-treat entire population, safety will be checked by recording the following adverse effects throughout the duration of the study: hypoglycemia, genital infections, urinary tract infections, excess osmotic diuresis signs (increased urinary frequency, mouth dryness, or polyuria), and hypovolemic symptoms. A previous study has reported an increased prevalence of hypoglycemia with sulfonylureas than with canagliflozin [14]. We therefore need to pay careful attention to the development of hypoglycemia, especially in patients assigned to the glimepiride group, despite this drug being initiated at a low dose in the study. If the investigators confirm these adverse effects, the grade of severity, treatment, outcomes, and relationship to the study drug will be assessed. The criteria for withdrawal from the trial are listed in Table 3. In addition, the incident of withdrawal from the study will be reported promptly to the Data and Safety Monitoring Board (DSMB) by the trial organizer.

**Table 3 Tab3:** Discontinuance criteria

Severe hypoglycemia that needs some support by family members or medical care at medical settings
Seriously poor glycemic control such as ≥HbA1c 10.0 %
Diabetic ketoacidosis
Dehydration
Considered inappropriate to continue the study by investigators due to aggravation of primary disease or complications
Considered inappropriate to continue the study by investigators due to adverse side effects of the study drug
Offer for participation declined by participants
Considered inappropriate to continue the study by investigators due to some other reason

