### Trial endpoints

NT-proBNP is used widely to monitor the therapeutic efficacy of agents for heart failure in clinical trials and is established as a prognostic biomarker for heart failure [21–23]. In addition, NT-proBNP-guided treatment for heart failure has been demonstrated to improve clinical outcomes in a randomized trial [24]. Therefore, the percent change in NT-proBNP levels from baseline to 24 weeks will be used as the primary endpoint in the CANDLE trial. The secondary endpoints are the values and changes in parameters after 24 weeks of treatment (or at discontinuation), including: (1) NT-proBNP, (2) glycemic control (HbA1c, fasting plasma glucose, plasma insulin, HOMA-R and HOMA-beta), (3) clinic systolic and diastolic BP and home BP (optional), (4) BW, (5) biochemical tests (lipid profiles and uric acid), (6) quality of life (MLHF scores) (7) echocardiographic cardiac function parameters (LVEF and E/e’) and severity and change in NYHA functional classification, and (8) renal function parameters (serum creatinine level, estimated glomerular filtration rate (eGFR), urinary albumin excretion, and urine L-FABP). Other secondary endpoints include clinical outcomes such as CV events, including all-cause death, non-fatal myocardial infarction, non-fatal stroke, hospitalization for heart failure, and changes in medications related to aggravation of heart failure. Safety endpoints include adverse effects and adverse drug reactions observed during treatment with the study drugs. The exploratory endpoints are changes in specific biomarkers after 24 weeks of treatment, including high-sensitivity troponin I, hsCRP, serum cystatin C, PTX3, RAGE, ANGPTL2, IL-8, and periostin. The findings of these biomarker assays may, in part, provide mechanistic insights on the effect of canagliflozin on CV pathogenesis.

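### Deaths and cardiovascular events are secondary endpoints, so the article sends them to an FAS without serious protocol violators; events can drop out of the randomised comparison of clinical outcomes

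*Protocol article*

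**What the plan says.** Four statements in the protocol article fix the populations.

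- **Trial endpoints** places the clinical events among the secondary endpoints: "Other secondary endpoints include clinical outcomes such as CV events, including all-cause death, non-fatal myocardial infarction, non-fatal stroke, hospitalization for heart failure". The list continues with medication changes for aggravated heart failure. A separate sentence covers safety: "Safety endpoints include adverse effects and adverse drug reactions observed during treatment with the study drugs". It names no population.
- **Analysis plan** sets the population for all secondary endpoints: "The analyses of the primary and secondary endpoints will be performed in the FAS, which includes all patients who received at least one dose". The patients must also be ones who "did not have any serious violation of the study protocol, and had data collected after commencement of treatment". No exception is made for clinical events.
- **Safety** uses a wider population: "Based on the intention-to-treat entire population, safety will be checked by recording the following adverse effects throughout the duration of the study: hypoglycemia", followed by "genital infections, urinary tract infections, excess osmotic diuresis signs (increased urinary frequency, mouth dryness, or polyuria), and hypovolemic symptoms". None of the clinical events is on this list.
- **Study overview and design** states the purpose: "This study tests the hypothesis that additional administration of canagliflozin to standard therapy does not worsen the pathological state of CHF". The Discussion repeats that the aim is safety together with non-inferiority.

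**The concern.** Read together, these statements compare mouth dryness in everyone randomised, but compare death and heart-failure admission in a subset chosen after randomisation. That is the reverse of what a trial about safety in heart failure would want. An adjudicated event can be counted whether or not the patient kept to the protocol, so a violation gives no reason to discard it.

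Excluding violators also breaks the randomised comparison, and violation need not be equally likely in the two arms. Treatment is open-label, and the Discussion concedes possible bias from physicians' treatment choices. Table 2 prohibits different drugs in each arm. Under Randomization and treatment, a patient already on a sulfonylurea has to stop it in the canagliflozin arm but may move to glimepiride in the other, so the opportunities for violation are not symmetric. With 125 patients per arm and 24 weeks of treatment, events may be few, and one or two omitted events could then change the impression the comparison gives.

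**Working it through.** The article gives no event rate and no expected number of FAS exclusions, so there is no plan figure to reproduce on this point. The stated 125 per group is sized for NT-proBNP and serves here only as the arm size.

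**Step 1: follow the rule through the text.**

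| Outcome | Class in Trial endpoints | Population that follows |
|---|---|---|
| Listed tolerability effects | Safety | Intention-to-treat (Safety section) |
| Other adverse effects during treatment | Safety | Not named |
| Death, infarction, stroke, heart-failure admission, heart-failure drug changes | Secondary | FAS (Analysis plan) |

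Endpoint adjudication provides for blinded review of events and for safety monitoring. It does not set the population for the between-group comparison, and no other section moves the events to intention-to-treat.

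**Step 2: which exclusions can lose an event?**

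- *Serious violation*: yes, whenever the event occurs. This is the firmest route.
- *No dose*: yes, for events in patients randomised but never treated.
- *No data after the start of treatment*: doubtful, because a recorded event after the first dose can itself be such data.

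**Step 3: illustrate the size. All inputs except 125 are assumptions.** Let p be the 24-week event risk inside the FAS (2% to 8%), x the fraction outside it (5% or 10%), and k the event risk outside the FAS relative to inside (1, 2 or 4).

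- Events in the arm = 125 × p × (1 − x + xk)
- Events omitted = 125 × x × k × p
- Share omitted = xk / (1 − x + xk)
- FAS risk ÷ risk in all randomised = 1 / (1 − x + xk)

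| x | k | Share omitted | FAS risk ÷ true risk |
|---|---|---|---|
| 5% | 1 | 5.0% | 1.00 |
| 5% | 2 | 0.10/1.05 = 9.5% | 0.95 |
| 5% | 4 | 0.20/1.15 = 17.4% | 0.87 |
| 10% | 1 | 10.0% | 1.00 |
| 10% | 2 | 0.20/1.10 = 18.2% | 0.91 |
| 10% | 4 | 0.40/1.30 = 30.8% | 0.77 |

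At the low end (p = 2%, x = 5%, k = 1), 125 × 0.05 × 0.02 = 0.125 of 2.5 events are omitted. At the high end (p = 8%, x = 10%, k = 4), 125 × 0.10 × 4 × 0.08 = 4 of 13 are omitted, and the arm reports 9/112.5 = 8.0% instead of 13/125 = 10.4%.

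**Step 4: direction.** Take equal true risks and the high-end row. If the loss occurs only on canagliflozin, a true risk ratio of 1.0 appears as 0.77. If it occurs only on glimepiride, it appears as 1/0.77 = 1.30. If x and k are equal in both arms, the factors cancel and the ratio stays at 1.0, though events are still lost. If k = 1, no bias arises at all.

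**The case against.** The best defence is that the FAS sentence was never meant for events. The article says secondary analyses follow the primary method, which is ANCOVA with least-square means. That does not suit event counts, so the sentence may be a catch-all, to be refined in the analysis plan still to be written. This is plausible, but the article does not leave the matter open. It names both populations, and an analysis plan that follows it inherits the narrower one for the events.

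Three stronger readings should be resisted.

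- *The serious harms vanish from safety reporting.* The general safety endpoint covers adverse effects during treatment, and a death or admission may be recorded there. Treating the Safety list as exhaustive is an inference. The supportable claim concerns the comparison of clinical events as secondary endpoints.
- *Events before the week-4 visit are lost.* The FAS asks only for data after treatment starts. It requires neither a visit nor a laboratory value, and an event after the first dose can satisfy it.
- *The rule favours canagliflozin.* Nothing in the article shows which arm would lose more events. A heart-failure event is also not shown to lead to use of a drug on the prohibited list.

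It is also fair to say that an all-treated population would cure the violator exclusion, and that adding never-treated patients can dilute a harm signal. Both points stand. They bear on the choice of remedy, not on whether violators should be dropped.

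**Conclusion.** The point holds in limited form. As written, the article compares its clinical events in a population that leaves out serious violators and never-dosed patients, while it gives intention-to-treat to a list that does not name those events. Loss is possible, not certain. It may differ by arm and could push the comparison either way. The document does not allow its size to be computed: the 5% to 31% range rests wholly on the assumed risks and exclusion rates, and the ratios of 0.77 and 1.30 also require loss in one arm only. The intention-to-treat population is taken to mean everyone randomised, which the article's wording suggests but does not spell out. The primary NT-proBNP test and the sample size are not touched. This is a cheap improvement worth making, not a flaw that invalidates the design.

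**What to change.** In Analysis plan, limit the FAS to the secondary endpoints that are measurements. Add one sentence: the adjudicated clinical events (death, infarction, stroke, heart-failure admission, and drug changes for worsening heart failure) are compared by randomised arm in the intention-to-treat population that the Safety section already uses, with no exclusion for protocol violation, counting all events recorded from randomisation to week 24 or last contact. Report the FAS result as supportive.

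The cost is one sentence and a change in denominators and events counted; the total stays at 250. Event evaluation and blinded adjudication are already planned. The article does not show that events are followed to week 24 after withdrawal, hence the wording about recorded events and last contact. The downside is that a few never-treated or violating patients enter the denominators and slightly dilute on-treatment rates; the supportive FAS result lets a reader see how much that matters.

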### Randomization and treatment

Eligible patients with the appropriately signed informed consent will be randomized to either the canagliflozin or glimepiride groups at a ratio of 1:1 using the minimization method with biased coin assignment balancing for age (<65, ≥65 year), HbA1c level (<6.5, ≥6.5 %), and left ventricular ejection fraction (LVEF; <40, ≥40 %) at the time of screening [18, 19]. The trial is an open-label design, although the assessor(s) will be blinded to treatment randomization. The assessors will also be blinded to the primary end point, NT-proBNP level, by measurement at a central laboratory.

All participants receive the study drug for 24 weeks. Patients who are assigned to the canagliflozin group receive canagliflozin 100 mg once daily. The EMPA-REG OUTCOME trial reported small dose-dependent effects of empagliflozin (10 mg vs. 25 mg/day) on metabolic parameters. However, the two dose groups had similar hazard ratios for cardiovascular outcomes [13]. Some studies on canagliflozin showed that 100 mg/day had sufficient effects on metabolic parameters, while 300 mg/day was slightly more effective [14, 15, 20]. Importantly, only 100 mg/day is approved in Japan, and therefore the dose of canagliflozin is fixed at 100 mg/day in the canagliflozin group. Because of the possible risk of excess diuresis and subsequent dehydration by combined use of canagliflozin and diuretics, the dose of the diuretics may need to be reduced when necessary. Patients assigned to the glimepiride group are started at a dose of 0.5 or 1.0 mg once or twice daily. According to the individual’s glycemic control, the dose of glimepiride can be increased to 6.0 mg/day. For background therapy in both groups, participants who have been receiving any SGLT2 inhibitor other than canagliflozin need to discontinue it at the start of the washout period, for 4 weeks, prior to receiving the study drug, canagliflozin or glimepiride. While, participants who have been taking a sulfonylurea need to stop taking it in the canagliflozin group and need to change to glimepiride (if needed) in the glimepiride group at the initiation of the study drug (Additional file 1). Because of the possible risk of excess diuresis and subsequent dehydration by combined use of canagliflozin and diuretics, the dose of the diuretics may need to be reduced when necessary.

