Although a specific numerical goal of HbA1c level is not set in this trial, all participants need to be treated to achieve a personalized goal recommended by the guidelines (details in Additional file 2) [7]. Drugs that must not be used in combination with the study drugs are listed in Table 2. Within the appropriate range of the therapeutic goal, the participant’s background treatment will be, in principle and if possible, unchanged during the trial interval. If participants cannot achieve their glycemic goal, co-administration of anti-diabetic agents other than SGLT2 inhibitors and sulfonylureas or increased dosages of the anti-diabetic agents other than the target agents in both groups may be initiated, with caution being taken to prevent the development of hypoglycemia. After the trial is completed, all participants can continue any anti-diabetic treatment in accordance with their individual condition.

**Table 2 Tab2:** Prohibited concomitant drugs

Canagliflozin group
SGLT2 inhibitors other than canagliflozin
Sulfonylureas
Pioglitazone
Glimepiride group
Sulfonylureas other than glimepiride
SGLT2 inhibitors
Pioglitazone

*SGLT2* sodium glucose cotransporter 2

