There are several limitations in the trial. First, the CANDLE trial is not a placebo-controlled trial. The aim of the trial is therefore to test the safety and non-inferiority of canagliflozin compared with glimepiride in T2DM patients with CHF. Second, as the trial is an open label design, there may be some bias towards the assessment of outcomes resulting from the physicians’ choice of treatment. However, there are strict definitions on the background treatment that will, in principle and if possible, remain unchanged during the trial interval. To overcome this possible bias, NT-proBNP, a primary endpoint, will be measured at a central laboratory, and all the data will be managed and statistically analyzed in a blinded manner. Finally, the trial interval of 24 weeks may be short to titrate the appropriate dose of glimepiride. According to a previous study from Japan that evaluated the safety and efficacy of glimepiride titration using self-monitoring blood glucose (SMBG) method [57], glimepiride treatment during 24 weeks resulted in a sufficient reduction in HbA1c level in the SMBG group and even in patients in the control group who were titrated empirically by their clinician without causing severe hypoglycemia. The average doses of glimepiride were 1.0 ± 0.8 mg/day in the SMBG group and 0.6 ± 0.3 mg/day in the control group, with no patient receiving glimepiride ≥3.5 mg/day. In addition, the HbA1c level at 24 weeks was significantly lower in patients receiving 0.5 mg/day compared with patients receiving >0.5 mg/day. This result indicates that glimepiride treatment for 24 weeks may not necessarily be too short to titrate glimepiride. Inappropriate titration of glimepiride may impact glycemic control and NT-proBNP levels in the glimepiride group, although there is currently insufficient evidence, as to whether or not, or the extent to which glimepiride treatment may affect NT-proBNP levels.

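### The full analysis set, the only population named for the primary non-inferiority test, excludes patients for serious protocol violations, including violations after randomisation

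*Protocol article*

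**What the plan says.** Under Analysis plan, the article states: "The analyses of the primary and secondary endpoints will be performed in the FAS". It names no other population for efficacy. Membership of the FAS has three conditions. The first covers "all patients who received at least one dose of treatment during the study period". The other two are that the patient "did not have any serious violation of the study protocol, and had data collected after commencement of treatment".

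Three other places bear on the point:

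- **Blinding.** Randomization and treatment says: "The trial is an open-label design, although the assessor(s) will be blinded to treatment randomization". The limitations paragraph of the Discussion adds that "all the data will be managed and statistically analyzed in a blinded manner".
- **Conduct rules by arm.** Table 2 bars all sulfonylureas in the canagliflozin group. In the glimepiride group it bars "Sulfonylureas other than glimepiride" and all SGLT2 inhibitors. Pioglitazone is barred in both. Canagliflozin is given at a fixed dose, whereas glimepiride may be titrated to glycaemic control.
- **Safety population.** Under Safety: "Based on the intention-to-treat entire population, safety will be checked".

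**The concern.** The conditions of at least one dose and some data after treatment start are usual for a full analysis set. The violation condition is not: it is what normally defines a per-protocol set. As printed it covers any serious breach at any time, so a patient can leave the primary analysis because of events after randomisation.

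In this trial both the patient and the treating physician know the treatment, and what counts as a breach depends partly on the arm. When glycaemia is poor, raising glimepiride is permitted in one arm, while adding a sulfonylurea is a breach in the other. If patients leave the two arms at different rates, and those who leave differ in NT-proBNP, the comparison is no longer the randomised one.

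The hypothesis is that canagliflozin does not worsen heart failure, judged against a ratio margin of 1.1. On the log scale that margin is about 0.095, so a modest selective loss is not negligible beside it.

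**Working it through.** **1. The plan's own figure.** Inputs from Sample size estimation: log-scale SD 0.80, margin 1.1, true difference 18% (ratio 0.82), one-sided alpha 2.5%, power at least 80%, dropout 10%, 125 per group.

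Formula: n per arm = 2 × SD² × (1.960 + 0.842)² / Δ².

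- With the margin taken as 0.10 on the log scale, Δ = 0.10 − ln 0.82 = 0.2985. This gives n = 113, and 113/0.9 = 125.6, so 126. (113 × 1.1 = 124.3, so 125.)
- With the margin taken strictly as ln 1.1, Δ = 0.0953 + 0.1985 = 0.2938. This gives n = 117, and 117/0.9 = 130.

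The stated 125 is therefore reproduced, to within one patient, on the first reading. The sample size is not in dispute here. It supplies about 113 analysed patients per arm for what follows.

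**2. Bias from selective exclusion.** Let f be the excess fraction excluded from one arm, and D the amount by which the mean log ratio of the excluded patients exceeds that of the retained patients. The retained mean then lies below the full-arm mean by f × D. Neither f nor D is given in the documents; both are assumptions.

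Take D = ln 2 = 0.693 (NT-proBNP ratio doubled) and compare with ln 1.1 = 0.0953:

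| f, canagliflozin arm only | Shift f × D | Share of margin |
|---|---|---|
| 5% | 0.05 × 0.693 = 0.035 | 36% |
| 8% | 0.08 × 0.693 = 0.055 | 58% |
| 10% | 0.10 × 0.693 = 0.069 | 73% |

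**3. Effect on the test.** Put the true effect exactly on the margin, with 113 per arm before exclusion. Then SE = 0.80 × √(1/[113(1 − f)] + 1/113), and the one-sided type I error is Φ(fD/SE − 1.960).

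- f = 5%, D = 0.693: SE = 0.108, so Φ(0.321 − 1.960) = 5.1% instead of 2.5%.
- f = 10%, D = 0.693: SE = 0.109, so Φ(0.634 − 1.960) = 9.2%.
- Over f = 2% to 10% and D = 0.4 to 0.8, the error runs from 3.0% to 11.0%.

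**4. The opposite direction.** If the same patients are lost from the glimepiride arm only, the sign of fD reverses. With D = 0.693 the error falls to 1.1% (f = 5%) and 0.5% (f = 10%). Over the same grid it runs from 2.1% down to 0.4%.

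**5. The conduct rules side by side.** Table 2 is largely a mirror image: each arm bars the other arm's class, other members of its own class, and pioglitazone. The main real difference is titration, which is open to glimepiride and not to canagliflozin. That makes unequal exclusion possible. It does not establish its size or direction.

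**The case against.** A reader might infer that the exclusions **are** unequal and favour canagliflozin. The documents do not support that. A glimepiride patient given an SGLT2 inhibitor is as much in breach as a canagliflozin patient given a sulfonylurea, and the remaining add-on options are the same in both arms. The most visible route to a breach follows glycaemia, while the endpoint is NT-proBNP, and the Discussion says evidence on whether glimepiride affects NT-proBNP is insufficient. Worsening heart failure is handled as an outcome or as a reason for discontinuation, and is not described as a violation. All of this stands, and it limits the point to a risk of unknown direction.

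A reader might also infer that no per-protocol analysis, no definition of a serious violation and no method for missing data will exist. That cannot be concluded. This is a condensed article, and it says an analysis plan will be written before recruitment ends and the database is locked.

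Nor is the whole-population safety assessment a defect. A wider set for safety than for efficacy is ordinary.

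Two mitigations are real: NT-proBNP is measured centrally, and data handling and analysis are blinded. They reduce the risk without removing it. Breaches arise from decisions made with treatment known, and the article does not say that their classification is blinded.

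Finally, keeping off-protocol patients can itself dilute a true difference and favour non-inferiority. That is a reason to report both sets. It does not justify merging them under the FAS name.

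None of these arguments changes the printed definition of the FAS.

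**Conclusion.** The point holds as a defect in text that the article fixes. The only population named for the primary non-inferiority test carries a per-protocol exclusion that is not limited to breaches present before randomisation. In an open-label trial with some arm-specific conduct rules, this can bias the result either way.

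The size is illustrative and rests wholly on assumed f and D: a third to nearly three quarters of the log margin for a net 5% to 10% excess exclusion of patients with doubled NT-proBNP. The 10% case equals the whole planned dropout placed in one arm and fully related to outcome, so it is an upper illustration and not a forecast. If exclusions are few, balanced or unrelated to NT-proBNP, the effect is negligible.

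Severity: should be fixed. The evidence does not support a claim that the trial is biased towards non-inferiority.

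**What to change.** - Delete the violation condition from the FAS, or limit it to eligibility breaches present before randomisation and judged blind to arm. Analyse the dosed patients as randomised.
- Move the violation criterion to a separate per-protocol set, with violations classified blind to arm before database lock.
- Report the non-inferiority result in both sets, so that any dependence on the exclusions is visible.

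The cost is a change of wording and one further run of the primary model. The analysis plan was still to be written when the article appeared, so the change could be made there. The downside is that some off-protocol data enter the FAS and may dilute a true difference; the per-protocol result alongside addresses that.

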### Trial population and recruitment

We aim to recruit a total of 250 participants across approximately 35 sites in Japan. Recruitment for this trial began in October 2015 and will be completed by December 2017. Eligible patients in the trial are T2DM patients with CHF (aged ≥20 years) who comply with all the enrollment criteria. The detailed inclusion and exclusion criteria are listed in Table 1. Briefly these criteria include: (1) Patients with appropriately diagnosed T2DM, who are drug-naïve or taking any anti-diabetic agent; (2) T2DM clinically requiring a start or change of an anti-diabetic agent; (3) complicating NYHA functional classification I to III CHF, but not IV, with maintenance of the clinical condition and unchanged medical treatment for CHF, including angiotensin-converting enzyme inhibitors, angiotensin II receptor blockers, beta-blockers, and diuretic agents for 4 weeks prior to screening. In the trial, CHF is classified comprehensively by skilled cardiologists using several findings, including clinical symptoms (the Framingham criteria for congestive heart failure and NYHA functional classification), history of hospitalization for heart failure, and clinical tests such as echocardiography and biomarkers. However, there is no limitation on the NT-proBNP level at enrollment. Prior to eligibility screening, every participant is required to receive an adequate explanation based of the trial plan, with written informed consent then being obtained from each patient.

**Table 1 Tab1:** Detailed inclusion and exclusion criteria

Inclusion	Exclusion
Adults (aged ≥20 years)	Type 1 diabetes mellitus
T2DM patients who need to start or who are possibly changing or adding an anti-diabetic agent	History of diabetic ketoacidosis, diabetic coma, or hypoglycemic attack ≤6 months prior to informed consent
CHF (NYHA functional classification I to III)	Severe renal dysfunction (eGFR <45 ml/min/1.73 m^2^) or patients receiving dialysis
Without change in NYHA functional classification or drugs for heart failure 4 weeks prior to eligibility	Severe liver dysfunction (at least threefold higher AST or ALT more than the upper limit of the facilities reference value
The patient provided written informed consent to participate in the study	CHF (NYHA functional classification IV)
	Patients with pituitary or adrenal dysfunction
	Patients with malnutrition, starvation, irregular eating pattern, lack of dietary intake, or debilitation

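### Recommended improvement: the primary ANCOVA leaves out baseline NT-proBNP, which is already measured, and so gives up precision; the planned test remains valid without it

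*Protocol article*

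**What the plan says.** All places are in the protocol article.

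- **Endpoint.** Trial endpoints: "the percent change in NT-proBNP levels from baseline to 24 weeks will be used as the primary endpoint".
- **Primary model.** Analysis plan: "To test for non-inferiority of the primary endpoint, the ANCOVA will be applied adjusted for age", followed by HbA1c and LVEF. Each factor enters as two categories, cut at 65 years, 6.5% and 40%. Baseline NT-proBNP is not listed, and no other section adds it.
- **Allocation.** Randomization and treatment: the minimisation uses the same three factors at the same cut-points. NT-proBNP is not one of them.
- **Entry.** Trial population and recruitment: "there is no limitation on the NT-proBNP level at enrollment", with NYHA classes I to III admitted.
- **Availability.** Measurements: NT-proBNP is assayed centrally at baseline and at the final visit.
- **Secondary endpoints.** Analysis plan: "The secondary analysis will be performed in the same manner as the primary analysis".

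**The concern.** A change score is generally correlated with its own baseline through regression to the mean: patients who start high tend to fall, and patients who start low tend to rise. If baseline is not in the model, that part of the variation stays in the residual and widens the confidence interval that is compared with the margin. Dichotomised LVEF, age and HbA1c are weak stand-ins for a continuous marker that every patient has measured.

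The article states the model for the primary test, so this is a choice that can be commented on, not detail left to an unseen analysis plan. At stake is some power, and a narrower interval in a trial whose non-inferiority margin is only 10% on the ratio scale. Since the secondary endpoints follow the same model, those analysed as change from baseline forgo the same kind of gain.

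**Working it through.** **Inputs from Sample size estimation:** SD of the log ratio 0.80; margin 1.1 (ln 1.1 = 0.0953); true difference 18%, read as a ratio of 0.82 (ln 0.82 = −0.1985); one-sided alpha 0.025; power at least 80%; 125 per group; dropout 10%.

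**Assumptions, not in the documents:** the analysis is on the log ratio, as in the sample size; log-variances are equal at baseline and week 24; the correlation rho between the two visits is 0.5, 0.7 or 0.9.

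**Step 1. The plan's own figure.** Distance from assumed truth to margin = 0.0953 + 0.1985 = 0.2938. By the normal approximation, n per arm = 2 × 0.80² × (1.960 + 0.842)² / 0.2938² = 116.4, so 117 evaluable, or 117/0.9 = 130 with dropout. If the margin is instead taken as 0.10 on the log scale, n is 113, and 113/0.9 gives 126. The stated 125 is therefore reproduced closely, from an unadjusted comparison.

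The text does not make clear whether 125 is before or after dropout, so both 125 and 125 × 0.9 = 112.5 evaluable per arm are carried forward. Unadjusted power (noncentral t) is 82.4% and 78.3% respectively.

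**Step 2. Effect of the covariate.** With equal variances, adjusting the log ratio for log baseline multiplies the residual variance by (1 + rho)/2, so the residual SD is 0.80 × √((1 + rho)/2). The unadjusted variance is larger than the adjusted one by a factor of 2/(1 + rho).

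| rho | Residual SD | Excess variance without covariate | Power, 112.5 per arm | Power, 125 per arm |
|---|---|---|---|---|
| not adjusted | 0.80 | – | 78.3% | 82.4% |
| 0.5 | 0.69 | 33% | 88.6% | 91.6% |
| 0.7 | 0.74 | 18% | 84.5% | 88.0% |
| 0.9 | 0.78 | 5% | 80.3% | 84.3% |

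A simulation of 4,000 trials per rho at 112 per arm agrees. Power without and with the covariate was 77.8% and 87.9% (rho 0.5), 78.1% and 83.8% (0.7), and 77.6% and 79.8% (0.9). Mean estimates were between −0.195 and −0.200 for both models, against a true value of −0.198, so neither is biased.

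**Step 3. Baseline spread and rho are tied.** With equal variances and a log-ratio SD of 0.80, rho = 1 − 0.64/(2 × SD_b²), where SD_b is the SD of log baseline.

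- SD_b 0.80: rho 0.50, adjusted power 88.6% at 112.5 per arm.
- SD_b 1.2: rho 0.78, power 82.9%.
- SD_b 1.5: rho 0.86, power 81.2%.

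At a fixed SD of 0.80, a wider baseline spread means less to gain.

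**Step 4. The same loss seen conditionally.** At 112.5 per arm the unadjusted standard error is 0.80 × √(2/112.5) = 0.107. A chance imbalance of one standard error in mean log baseline, SD_b × √(2/112.5), shifts the unadjusted estimate by (1 − rho) times that imbalance.

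| rho | SD_b | 1-SE imbalance | Shift | Shift / 0.107 |
|---|---|---|---|---|
| 0.5 | 0.80 | 0.107 | 0.053 | 0.5 |
| 0.7 | 1.03 | 0.138 | 0.041 | 0.4 |
| 0.9 | 1.79 | 0.239 | 0.024 | 0.2 |

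This is not a second cost. At rho 0.7, the unadjusted variance less the squared shift is 0.1067² − 0.0413² = 0.0097, whose root, 0.098, is the adjusted standard error 0.738 × √(2/112.5).

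**The case against.** The strongest reply is that nothing here is an error. Randomisation balances baseline NT-proBNP in expectation, the change score already removes part of any chance difference, and the planned interval already allows for the rest. The trial was sized on an unadjusted t test with SD 0.80, so its planned power never relied on this covariate. The model uses exactly the minimisation factors, so design and analysis agree. The list is not said to be exclusive, and the analysis plan was still to be written. All of this stands, and it is why the point is an improvement and not a defect. It does not remove the point: the stated primary model can be made more precise with data already collected.

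Three stronger readings are tempting and are not supported:

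- **The estimate is biased by baseline imbalance.** It is not biased on average. Setting the shift against ln 1.1 makes it look large: 0.041 is 43% of 0.0953. The fairer yardsticks are the standard error (about 0.4 of it at rho 0.7) and the assumed distance to the margin (0.041/0.294 = 14%). The shift is also the precision loss again, not an addition to it.
- **The open NT-proBNP entry range makes the omission costlier.** At the plan's SD of 0.80, Step 3 shows the reverse. Pairing a baseline SD of 1.2 with rho 0.7 would imply a log-ratio SD of 1.2 × √0.6 = 0.93, which is not the plan's figure.
- **The trial is underpowered without the covariate.** The 78.3% arises only if dropout is deducted from 125. With 125 evaluable per arm, unadjusted power is 82.4%. That ambiguity is separate from the choice of covariates.

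**Conclusion.** The point holds as a recommended improvement, not a must-fix. The named primary model omits the baseline value of its own outcome and gives up precision that would cost nothing to recover. Type I error, average bias and the stated sample size are unaffected. The gain in power is about 2 to 10 percentage points (rho 0.9 to 0.5), and a wide baseline spread puts it towards the low end. The omission itself is certain from the text. Its size is not, because it rests on an assumed rho, on equal log-variances at the two visits and on the plan's SD of 0.80.

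**What to change.** Before database lock, specify the primary model as ANCOVA of log(NT-proBNP at week 24 / baseline) on treatment, continuous log baseline NT-proBNP and the three minimisation factors. For each continuous secondary endpoint, add that endpoint's own baseline value to its model.

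The cost is one sentence in the analysis plan, with no new patients or measurements. The article says the plan will be written before recruitment ends and before database lock, so the covariate can still be prespecified. Added after a baseline imbalance has been seen, it would look data-driven, which matters more in an open-label trial.
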